### Data management {19}

Each participant will be dealt a study number which further is used for identification. A specific key file is created for the identification, where personal identity numbers and study numbers are stored. This key file will only be kept at a hospital computer belonging to the local principal investigator. All examination results and medical considerations are documented in the medical chart. This is protected by the Swedish Law of Secrecy and Public Access. A CRF for each patient and all entered screening instruments (Tables 1 and 2) are obtained and held in a project-specific database and in patient-specific study binders.

There is no double data entry. Members of the steering committee intermittently conduct internal monitoring where the quality of entered study data is assessed. Likewise, an assessment of adherence to the protocol is conducted during these meetings. Adherence to the individual recommendations made by the health care professionals during the intervention is assessed during the weekly follow-up meetings (see item 11c).

### Confidentiality {27}

The key file is kept at a hospital computer belonging to the local principal investigator who is responsible for the collected personal data. The information is kept in accordance to the EU Data Protection Regulation. The information will only be shared with the project steering group. The information will be kept for 10 years and will not be disclosed to a third party. Processing of personal data will be done according to GDPR and in concordance with the Swedish Law of Secrecy and Public Access. Participants can, at any time, request their data to be retracted from the database. Likewise, participants are authorized to correct, delete or restrict the use of their information, at any time.

### Plans for collection, laboratory evaluation and storage of biological specimens for genetic or molecular analysis in this trial/future use {33}

Not applicable, no biological specimens will be kept in the trial.

## Statistical methods

### Statistical methods for primary and secondary outcomes {20a}

The primary analysis will be performed according to “intention to treat”. As a secondary analysis, a per-protocol analysis will be made. The dataset will be closed, an analysis plan will be made and a multivariate analysis with relevant confounding factors will be performed.

QALYs are calculated by multiplying the health care state with the patient’s survival time at 12 months. The HRQoL is considered linear between 2 values (index and 12-month follow-up). If a person dies during follow-up, the HRQoL at index is carried forward to the time of death. If only HRQoL at index is available (missing data at the 12-month follow-up), the score is carried forward, and, conversely, if only the 12-month follow-up score is available (i.e. data missing at index), this score is carried backward to the index. If a person dies during the index care episode, the QALY is set to 0. Adjusted data regarding costs and effects might be used in the cost-effectiveness analysis. Adjustments are done for age, sex and CCI.

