#### Outcomes and measurements

*Hospital stays and discharge destination*, data regarding the length of hospital stay, total number of hospital days within 3 months after discharge, discharge destination and use of home help services and 30-day readmission rates for all participants is collected from patient medical records.*Dependence*, evaluation of the level of independence/dependence in an elderly individual is of great importance for example when establishing the need of home help services or other assistance. This is assessed using the activities of daily living (ADL)-staircase, which is a validated and commonly used instrument. The screening results in a score from 0 to 9, where 0 is completely independent and 9 is completely dependent [42, 43]. A clinically significant change is defined as a change of minimum 1 step in any direction on the ADL-staircase. ADL-function is assessed at baseline and at post-op visit (approximately 2 months post-surgery). The patients are assessed by a physiotherapist or a study nurse at baseline and follow-up.*Physical function*, the physiotherapists are also using hand grip strength (HGS) and six-minute walk test (6MWT) to make an overall assessment of the patient’s physical status to establish individual recommendations on physical activity and exercise. Both HGS and 6MWT have previously been used in assessments of frail elderly patients [44, 45]. The tests are performed at baseline and not at follow-up and are only conducted on patients in the intervention group as part of the CGA and care intervention.*Nutrition*, malnutrition is common in the elderly population, especially if hospitalized, living in nursing facility or having home help services. Malnutrition is often unrecognized if not specifically targeted. The Mini-Nutritional Assessment-Short Form (MNA-SF) is a validated instrument for nutritional screening in frail elderly individuals. It renders a score which places the patients in one of three groups: normal nutritional status, at risk of malnutrition or malnourished [46, 47]. A clinically significant change is defined as a change in group classification. The patients in the intervention group are screened by a dietician at baseline and by a ward nurse or a dietician at the day of/day before surgery. The patients in the control group are screened by a study nurse at both measurements.*Medication safety*, polypharmacy and the use of potentially inappropriate medications is a growing issue in the elderly population. There is often a need of reviewing and altering an elderly individual’s prescribed medications to reduce the risk of adverse drug reactions and to enable beneficial pharmacological treatments [48–50]. The Safe Medication Assessment (SMA), including a review of the current list of medications [51], is used as a basis for assessing the individual patient’s medications in the trial. The instrument renders a score of 0–30, where a higher score indicates a safer treatment. A clinically significant change is defined as a shift of minimum 1 point in either direction. The questionnaire is filled out by a study nurse at baseline and at revisit, for all participants. To identify adverse drug reactions (ADRs), underuse of evidence-based drug therapy and effects of inappropriate medications, scoring scales [49, 50] and clinical judgements based on medical records will be used. These judgements will be retrospectively performed by senior clinicians [52].*Cognition*, a decline in cognitive function is naturally present in the ageing process. Some elderly individuals are experiencing a more pronounced decline, resulting in cognitive impairment or dementia [53]. In the trial, the Mini-Mental State Examination (MMSE) is used as a screening instrument of cognitive function at baseline. It is a validated and reliable assessment tool in screening for cognitive impairment [54]. The screening is performed by a study nurse at baseline for all participants, but the measurement is not done at follow-up.*Frailty* is an independent risk factor of adverse health outcomes and death [21] and also a predictor of increased hospital and health care costs [25]. The degree of frailty is assessed using the Clinical Frailty Scale (CFS-9). The scale ranges from 1, “very fit”, to 9, “terminally ill”. The scale has been validated and proven to be of prognostic value in clinical practice [26, 55, 56]. The estimates are performed by a study nurse at baseline and at revisit, for all participants. A clinically relevant change is defined as a shift of minimum 1 step on the scale. During the initial phase of the trial’s recruitment, a revision of the CFS-9 scale was made, including minor adjustments in the description of the different levels of frailty [57]. Before the updated version (v 2.0) was put into use, a new application to the Swedish Ethical Review Authority was made and was approved on 2021-05-31.*Complications*, postoperative complications are common in elderly patients undergoing colorectal cancer surgery. The complications can result in additional treatments, reoperations, the need of intensive care and death [7, 8]. The Clavien-Dindo classification is a validated and clinically relevant instrument for identifying and grading adverse postoperative events [58]. The postoperative complications are assessed by a physician based on data from the medical records at the time of revisit, for all participants.*Comorbidity*, the patient’s comorbidity is valued through the Charlson comorbidity index (CCI). The instrument is used to assess the total burden of disease and predicts a 10-year mortality for a patient, by using 19 categories of comorbidities. Each condition is given a grade of 1, 2, 3 or 6, based on the risk of death associated with the specific comorbidity [59, 60]. The CCI index estimate will be performed by a physician, based on data from the medical records at baseline and at revisit, for all participants.*Health-related quality of life (HRQoL)*. The instrument EuroQoL-5D-5L (EQ-5D-5L) is used to assess HRQoL in the trial. The tool consists of a questionnaire containing five health dimensions with five response levels and of a visual analogue scale (VAS) where the patient estimates their own overall current health. Each estimated score is represented by an index value which is derived from a pre-defined value set [61, 62]. The assessments are overseen by a study nurse at baseline and at follow-up (2 and 12 months), for all participants.*Health economical calculations*. A health care system perspective will be applied including hospital and primary care. Cost-effectiveness will be analysed based on mortality and HRQoL data (quality-adjusted life years [QALYs]) and costs of hospital care and primary care at baseline, 2 and 12 months post-surgery. An incremental cost-effectiveness ratio (ICER) is calculated regarding cost/QALY gained. QALYs are calculated by multiplying the health state value with the patient’s survival time at 12 months; see also the “Statistical methods for primary and secondary outcomes” section. Data regarding health care costs will be collected and documented for all participants at 2 months and 12 months from baseline. Hospital costs will be obtained from the Swedish Cost-per-Patient database [63] and from hospital-specific administrative systems. Primary health care costs will be collected from the administrative regional health care database in Västra Götalandregion (VEGA) [64] and by the use of models and actual health care contacts.*Mortality*, mortality data will be extracted from patient medical records and cross-checked against the Swedish Population Registry regarding all participants at 2, 3 and 12 months from baseline.

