## Data collection and management

### Plans for assessment and collection of outcomes {18a}

Data regarding the following outcomes: length of hospital stay and total number of hospital days, discharge destination, 30-day readmission rates, ADL performance, safe medication assessment and medication lists, CFS-9 score, postoperative complications and HRQoL are documented on the CRFs at baseline and at the postoperative visit. Data regarding mortality at 3 and 12 months will be collected and documented separately. Data needed for the health economical calculations and cost-effectiveness analysis; health care costs at 2 months and 12 months, HRQoL at baseline, 2 and 12 months follow-up and mortality data at 2 and 12 months will be collected and documented separately. A more detailed description of the data collection and the study instruments, along with their reliability and validity, are found under the “Outcomes {12}” section. The CRFs used for the control versus intervention group, in English versions, are attached to this article as Additional files 3 and 4.

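### The QALY rule uses only the index and 12-month EQ-5D-5L and leaves out the 2-month value, which the same protocol names as an input to the cost-effectiveness analysis

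*Protocol article*

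**What the plan says.** Three parts of the protocol article bear on this.

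- **What is collected.** Tables 1 and 2 schedule the EQ-5D-5L at baseline, at the postoperative visit (about 2 months) and at 12 months, in both arms. Outcomes and measurements confirms it: "The assessments are overseen by a study nurse at baseline and at follow-up (2 and 12 months), for all participants".
- **What the cost-effectiveness analysis needs.** Section {18a} lists, among the data for the health economic calculations, "HRQoL at baseline, 2 and 12 months follow-up and mortality data at 2 and 12 months". The abstract describes the same three HRQoL time points. The endpoint list in {12} gives baseline, 2 and 12 months for cost-effectiveness, although there the time points could be read as belonging to the costs alone.
- **How the QALY is computed.** Section {20a} opens with health state multiplied by survival time, then says how the state runs over time: "The HRQoL is considered linear between 2 values (index and 12-month follow-up"). For deaths: "If a person dies during follow-up, the HRQoL at index is carried forward to the time of death". A missing 12-month score is replaced by the index score. If the index score is missing and the 12-month score is present, "this score is carried backward to the index".

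On timing, {12} and the first part of the health economics paragraph place the time points after surgery. The same paragraph then says that cost data are collected "at 2 months and 12 months from baseline".

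**The concern.** Section {20a} is an explicit rule, not a gap that an analysis plan would fill, and it disagrees with the protocol's own description of the endpoint. Followed as written, it discards a measurement made in every patient who attends the postoperative visit. That measurement is the one closest to surgery, where a preoperative intervention could plausibly separate the arms before they converge. Any such temporary difference would be absent from the QALY difference and so from the denominator of the ICER.

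The filling rules have the same weakness: they use the index value even when a later, observed value exists. They also enter single filled-in values as if observed, which understates uncertainty. Section {20b} mentions sensitivity analyses in general terms, but none for the QALY.

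**Working it through.** The plan states no QALY or utility figure, so there is none to reproduce. All utilities below are assumed for illustration. Write u0, u2 and u12 for the values at index, 2 and 12 months, with a 12-month horizon in years.

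**Weights**

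- Stated rule: (u0 + u12)/2, so the weights are 1/2, 0, 1/2.
- Three-point area: (u0 + u2)/2 × 2/12 + (u2 + u12)/2 × 10/12. Collecting terms gives u0 × 1/12 + u2 × 1/2 + u12 × 5/12.
- The weight on the middle value is half the whole span, (2/12 + 10/12)/2 = 1/2. It does not depend on the visit falling at exactly 2 months.

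**Error for a survivor with all three values**

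Stated minus three-point = 5/12 × u0 + 1/12 × u12 − 1/2 × u2 = 0.5 × (straight-line value at 2 months − observed u2).

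Example with u0 = 0.70, u2 = 0.60, u12 = 0.70: stated 0.700, three-point 0.650, overstatement 0.050. With u2 = 0.50 the overstatement is 0.100.

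**Between-arm difference, arms equal at index and 12 months, difference d at 2 months**

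| assumed d | three-point QALY difference (0.5 × d) | stated rule |
|---|---|---|
| 0.02 | 0.010 | 0 |
| 0.05 | 0.025 | 0 |
| 0.10 | 0.050 | 0 |
| 0.15 | 0.075 | 0 |

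**When the loss is smaller**

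- Same dip in both arms (0.70, 0.60, 0.70 in each): each arm is overstated by 0.050, and the difference between survivors is 0 under either rule.
- Difference of 0.10 at both 2 and 12 months: three-point 0.5 × 0.10 + 5/12 × 0.10 = 0.092; stated 0.5 × 0.10 = 0.050. Just over half is kept.

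**Filling rules, per affected patient (u0 = 0.70, u2 = 0.60)**

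- Death at 6 months: stated 0.70 × 6/12 = 0.350. Using the 2-month value: 0.65 × 2/12 + 0.60 × 4/12 = 0.308. Difference 0.042.
- 12-month value missing: stated 0.700. Carrying the 2-month value: 0.65 × 2/12 + 0.60 × 10/12 = 0.608. Difference 0.092. If 5% of an arm were affected (the plan's loss figure, borrowed as an assumption), this averages 0.05 × 0.092 ≈ 0.005 QALY per patient in that arm.

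**The case against.** The strongest reply is that little of the trial depends on this rule. The QALY is one of ten secondary endpoints. HRQoL at follow-up against baseline is a separate endpoint, set at 2 months in the abstract, so the 2-month value is still analysed. Survival also still drives the QALY. The planned fall in 90-day mortality from 15% to 5%, at an assumed utility of 0.70 and about 0.9 year gained, is worth 0.10 × 0.70 × 0.9 ≈ 0.06 QALY, most of which the stated rule keeps. All of this stands and limits the consequence, but none of it removes the contradiction.

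It can also be said that the missing-data rule applies only where index is the sole score available. On that reading a patient with index and 2-month scores has no rule at all, and the 2-month value is still unused.

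A reader might infer more than the documents support:

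- *That the ICER denominator must be wrong.* It is a between-arm difference, distorted only if the arms depart differently from the straight line.
- *That the trial loses sight of recovery.* The Objectives section measures recovery through complications, which have their own endpoint.
- *That setting the QALY to 0 for a death in the index care episode favours one arm.* That episode is not defined in the article. If it means the surgical admission, little time is lost.
- *That everything should be counted from randomisation.* Control measurements are made at admission before surgery and follow-up visits are timed after surgery, so the data do not fit that clock.
- *That leaving baseline utility out of the adjustment is an error.* The text says "Adjustments are done for age, sex and CCI", but adjusted data are only a possibility there, and covariate choice is normally left to the analysis plan.

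**Conclusion.** The point holds as a contradiction with a calculable consequence. The QALY rule in {20a} omits a value that the abstract and {18a} make an input and that both arms provide. In the three-point area that value would carry half the weight.

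The loss is 0.5 × d QALY per survivor for a 2-month utility difference d that has vanished by 12 months: 0.010 to 0.075 for assumed d of 0.02 to 0.15. At d = 0.10 the loss of 0.05 is of the same order as the QALY gain from the planned mortality effect under the assumptions above. It shrinks if the difference persists, and it is nil for survivors if both arms dip alike. The filling rules matter less. Deaths before the 2-month visit are unaffected, because no 2-month value exists for them.

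The result assumes piecewise-linear utility and a 12-month horizon starting at index. That start is itself unsettled, since the text counts from baseline in one place and from surgery in another. The primary endpoint and the separate HRQoL endpoint are not touched. This should be corrected, but it does not threaten the trial's main conclusion.

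**What to change.** In {20a}:

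1. Define the QALY as the area under the curve through index, 2 and 12 months.
2. For deaths after the 2-month visit, carry the last observed value to the date of death and use 0 afterwards.
3. Where the 12-month value is missing, use the 2-month value, preferably through multiple imputation. Keep the index carry-forward and the carry-backward rules only as sensitivity analyses.
4. State one time origin for costs and QALYs, reconciling the wording in {12} and in the health economics paragraph, so that both cover the same period. The choice must fit when the index measurement is taken in each arm: at the intervention day in one, at admission before surgery in the other.

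Adding baseline utility to the age, sex and CCI adjustment is an optional refinement.

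The cost is revised wording and modest programming. The EQ-5D-5L is already scheduled at all three points in both arms, so no new data are needed for items 1 to 3. The change can be made before the dataset is closed.

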**Methods:**

This randomized controlled multicentre trial aims to investigate if CGA and care prior to curatively intended surgery for CRC in frail elderly patients will improve postoperative outcome. All patients ≥ 70 years with surgically curable CRC will be screened for frailty using the Clinical Frailty Scale (CFS-9). Frail patients will be offered inclusion. Randomization is stratified for colon or rectal cancer. Patients in the intervention group are, in addition to standard protocol, treated according to CGA and care. This consists of individualized assessments and interventions, established by a multiprofessional team. Patients in the control group are treated according to best known practice as stipulated by Swedish colorectal cancer treatment guidelines, within an enhanced recovery after surgery (ERAS) setting. The primary outcome is 90-day mortality. Secondary outcomes are the length of hospital stay and total number of hospital days within 3 months, discharge destination, 30-day readmission, ADL, safe medication assessment, CFS-9 score, complications, Health-Related Quality of Life (HRQoL) at 2-month follow-up in comparison to baseline measurements, health economical calculations including cost-effectiveness analysis based on costs of hospital care and primary care, mortality and HRQoL at baseline, 2- and 12-month follow-up and all-cause 1-year mortality.

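### The QALY rule gives the 2-month EQ-5D-5L no weight, although the protocol lists it as an input to the cost-effectiveness analysis and collects it in both arms

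*Protocol article*

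**What the plan says.** Section {20a} of the protocol article defines the QALY: "QALYs are calculated by multiplying the health care state with the patient’s survival time at 12 months". It then fixes the path between measurements: "The HRQoL is considered linear between 2 values (index and 12-month follow-up"). Two further rules in that section follow the same pattern. For deaths: "If a person dies during follow-up, the HRQoL at index is carried forward to the time of death". For a missing last score: "If only HRQoL at index is available (missing data at the 12-month follow-up), the score is carried forward". A death during the index care episode scores a QALY of zero. None of these rules mentions the 2-month score.

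Elsewhere the 2-month score belongs to this analysis. Section {18a} lists what the health-economic calculations require, including "HRQoL at baseline, 2 and 12 months follow-up and mortality data at 2 and 12 months". The Abstract (Methods) bases the same analysis on costs and on "mortality and HRQoL at baseline, 2- and 12-month follow-up". Tables 1 and 2 schedule EQ-5D-5L at baseline, at the postoperative visit (about 2 months after surgery) and at 12 months, in both arms.

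**The concern.** The trial tests whether geriatric assessment and care before surgery improves outcome and recovery afterwards. The 2-month visit is where section {11a} has postoperative recovery evaluated, so it is a natural place for quality of life to differ between the arms. A straight line from index to 12 months passes over whatever happens in between. If utility dips after surgery and then returns, the written rule overstates QALYs, and does so more in the arm with the deeper dip.

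The weight taken from the 2-month score goes mostly to the index score, which precedes any benefit of the intervention. Costs up to 2 months do enter the numerator of the ICER, while 2-month utility does not enter its denominator. The article also contradicts itself, because one section calls for the 2-month score in this analysis and another leaves it unused.

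**Working it through.** **Plan's own figure.** The article gives no numerical QALY and no utilities, so there is none to reproduce. All utilities below are assumptions. Index is taken to mean the baseline measurement.

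**Step 1: weights for a patient alive at 12 months with all scores observed.** Let U0, U2 and U12 be the scores at 0, 2 and 12 months.

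- Written rule: QALY = (U0 + U12)/2. Weights are 1/2, 0, 1/2.
- Three-point area: QALY = (U0 + U2)/2 × 2/12 + (U2 + U12)/2 × 10/12. Weights are 1/12, 1/2, 5/12.

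With the middle visit at month t of a 12-month span, the weights are t/24, 1/2 and (12 − t)/24. The middle weight stays at 1/2 for any t. The outer two shift: at t = 4, for example, they are 1/6 and 1/3.

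**Step 2: a difference d at 2 months that has closed by 12 months.** The three-point area gives 0.5 × d. The written rule gives 0.

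| Assumed d | Three-point area | Written rule |
|---|---|---|
| 0.02 | 0.010 | 0 |
| 0.05 | 0.025 | 0 |
| 0.10 | 0.050 | 0 |
| 0.20 | 0.100 | 0 |

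Example for d = 0.10: both arms have 0.70 at 0 and 12 months, with 0.55 (control) and 0.65 (intervention) at 2 months. The three-point area gives 0.625 and 0.675. The written rule gives 0.700 in both arms.

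**Step 3: a difference of 0.10 present at both 2 and 12 months.** Written rule: 0.10 × 1/2 = 0.050. Three-point area: 0.10 × (1/2 + 5/12) = 0.092.

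**Step 4: the death and missing-score rules.** Assume an index score of 0.70 and an observed 2-month score of 0.50.

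- Death at 6 months. Written rule: 0.70 × 6/12 = 0.350. Using the 2-month score and carrying it to death: (0.70 + 0.50)/2 × 2/12 + 0.50 × 4/12 = 0.267.
- 12-month score missing, patient alive. Written rule: 0.700. Using the 2-month score: (0.70 + 0.50)/2 × 2/12 + 0.50 × 10/12 = 0.517.

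**Step 5: scale.** Section {14} plans for 90-day mortality of 15% against 5%, a difference of 0.10. With utility 0.70 and the averted deaths otherwise at month m, the written rule credits 0.10 × 0.70 × (1 − m/12) QALY per patient. This is 0.0525 at m = 3, 0.061 at m = 1.5, and 0.070 if the deaths fall in the index episode and score zero. A transient 2-month difference of 0.05 to 0.10 (0.025 to 0.050 QALY per survivor) is thus of a similar order to the planned survival effect.

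**The case against.** A reader might infer that recovery contributes nothing to the cost-effectiveness result. The article does not support that. The ICER is cost per QALY gained, and its costs include "costs of hospital care and primary care at baseline, 2 and 12 months post-surgery", which would reflect stay, readmission and treated complications. Survival time enters directly, an index-episode death scores zero, and a utility difference still present at 12 months is counted, although at reduced weight. What is lost is utility information at 2 months, and only from the QALY term.

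The 2-month EQ-5D-5L is also not lost to the trial, since quality of life at follow-up against baseline is a separate secondary endpoint. The primary endpoint and the sample size are unaffected. These limits stand.

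The size depends on assumed utilities, and the zero in Step 2 arises because the 12-month scores are set equal. Hence the range, and the persistent case in Step 3. The three-point area is itself an approximation: it assumes that a gap at 2 months closes evenly over the following ten, so a faster closure would make the true loss smaller.

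One could argue that the two-point sentence is shorthand for interpolation between neighbouring measurements. The text does not allow this reading. The parenthesis names index and 12 months, and the missing-data rule treats a missing 12-month score as leaving the index score alone. Nor can the matter simply be left to a later analysis plan, because the article already states the rule.

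The contradiction rests on the Abstract and section {18a}. The sentence on the timing of costs does not prove it, and the QALY definition in Outcomes and measurements ("QALYs are calculated by multiplying the health state value with the" survival time) does not conflict with section {20a}.

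**Conclusion.** The point holds in limited form. As written, the 2-month EQ-5D-5L has weight 0 in the QALY, against 0.5 under a three-point area over the same 12 months. That contrast depends neither on the utilities nor on the exact visit date. The written rule also conflicts with the article's own list of inputs.

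A transient difference d costs 0.5 × d QALY per 12-month survivor: 0.010 to 0.100 for the assumed range of 0.02 to 0.20. A difference of 0.10 that persists is counted as 0.050 instead of 0.092. The outer weights of 1/12 and 5/12 assume the visit falls 2 months after index and will move with the actual date. The defect is confined to one component of a secondary endpoint, but it should be corrected before the dataset is closed.

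**What to change.** In section {20a}, replace the interpolation sentence with wording such as: *QALYs are the area under the EQ-5D-5L index values at baseline, 2 months and 12 months, linear between adjacent measurements, with the same time origin in both arms.*

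State that origin. Baseline is measured on the intervention day in one arm and at admission for surgery in the other, and the article counts follow-up from baseline in some places and from surgery in others. Using actual dates without a common origin would give the arms different spans.

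Change the rules for death during follow-up and for a missing 12-month score so that they use the last observed value, including the 2-month value, instead of always the index value. Check the rule for a missing index score in the same way. Align the QALY description under Outcomes and measurements. Keep the two-point calculation as a sensitivity analysis.

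The cost is a short text amendment covering the interpolation, the carry-forward rules and the time origin. It needs no new data, since the 2-month score is already collected in both arms.

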### Methods in analysis to handle protocol non-adherence and any statistical methods to handle missing data {20c}

The intention-to-treat (ITT) principle will be applied.

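### The QALY rules value late deaths and non-returners at the pre-operative EQ-5D score and leave out the 2-month score, which can bias the QALY difference and the ICER

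*Protocol article*

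**What the plan says.** Item 20a of the protocol article sets out the QALY calculation in full:

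- Shape: "The HRQoL is considered linear between 2 values (index and 12-month follow-up" being the two points named.
- 12-month score missing: "If only HRQoL at index is available (missing data at the 12-month follow-up), the score is carried forward".
- Death after the index episode: "If a person dies during follow-up, the HRQoL at index is carried forward to the time of death".
- Index score missing: "if only the 12-month follow-up score is available (i.e. data missing at index), this score is carried backward to the index".
- Death in the index episode: "If a person dies during the index care episode, the QALY is set to 0".

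The schedule supplies a third measurement. On EQ-5D-5L, Outcomes and measurements says: "The assessments are overseen by a study nurse at baseline and at follow-up (2 and 12 months), for all participants". The Abstract, Outcomes {12} and item 18a all list 2-month HRQoL among the data for the cost-effectiveness analysis. Item 18b adds that patients who do not appear at follow-up are checked for vital status only, so some known survivors will have no later score.

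**The concern.** A fill that copies the index score says that a frail patient's health did not change after major surgery. The rules apply it to two groups in whom that is least safe: patients who die between discharge and 12 months, and survivors who do not return. Survivors with a 12-month score do have their change counted, so patients are valued on different footings according to whether they died or responded.

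The rules also pass over data the trial collects for this purpose. The death rule does so without condition: a patient with a poor 2-month score who dies at month 6 is still credited with pre-operative health for six months. For survivors the wording is ambiguous. It could mean that no later score of any kind exists, although the parenthesis defines the trigger as a missing 12-month score.

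At stake are the QALY difference and the ICER, whose denominator it is. Late deaths are not rare: Sample size {14} cites one-year mortality above 20% in frail patients, though some of these deaths fall in the index episode and score 0.

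**Working it through.** **The plan's own figures.** No figure is stated for the QALY analysis. The one design figure, 170 per group, concerns 90-day mortality. It is reproduced by 15% against 5%, two-sided 0.05 (sidedness assumed), 80% power and a continuity correction: 160 per group, and 160/0.95 = 168.4, so 169. It has no bearing on this point.

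**Assumed inputs.** The documents give no EQ-5D values. I take index = 0.70, read as the pre-operative baseline because the article does not define it explicitly. Later scores are 0.60, 0.50 or 0.40, that is, declines d of 0.1, 0.2 or 0.3.

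**1. Survivor, 12-month score missing, two-point rule.** Rule: 0.70 × 1 = 0.700. Had the score been seen: (0.70 + later)/2. The overstatement is d/2.

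- Later 0.60: 0.650, overstated by 0.05
- Later 0.50: 0.600, overstated by 0.10
- Later 0.40: 0.550, overstated by 0.15

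For a patient who improved, the sign reverses.

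**2. Survivor, index missing.** With a true index of 0.70 and 0.50 at 12 months, carry-back gives 0.500 against (0.70 + 0.50)/2 = 0.600. The patient who declined is understated by 0.10; one who improved would be overstated.

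**3. Death at month 6.** Rule: 0.70 × 6/12 = 0.350. Using an assumed 2-month score of 0.50 and holding it to death: (0.70 + 0.50)/2 × 2/12 + 0.50 × 4/12 = 0.100 + 0.167 = 0.267. The excess is 0.083. In general it is d × (1/12 + 4/12) = d × 5/12, so 0.042 for d = 0.1 and 0.125 for d = 0.3.

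**4. Ranking of a late death against survival.** Death at month 11 scores 0.70 × 11/12 = 0.642. A survivor who ends at 0.50 scores 0.600. The break-even is 12 × 0.600/0.70 = 10.3 months, so with these values only deaths after that point outrank the survivor.

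**5. Arm level (item 1 only).** Mean overstatement in an arm = share missing × d/2.

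- 5% missing: 0.0025 (d = 0.1) to 0.0075 (d = 0.3)
- 20% missing: 0.010 to 0.030
- Between-arm bias if missingness differs by 10 points: 0.10 × d/2 = 0.005, 0.010 or 0.015 QALY for d = 0.1, 0.2 or 0.3

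**The case against.** The best defence is one of scope and size. The rules serve one secondary endpoint. Their bias is not all one way, and if missingness and decline are alike in both arms, the overstatement in survivors largely cancels in the difference. The only loss figure in the article is 5%, although it belongs to the sample size for 90-day mortality and not to the 12-month questionnaire. That non-return tracks decline is plausible but assumed. All of this stands, and it limits the point to a possible bias of modest average size.

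Four stronger readings are tempting and are not supported:

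- **That the confidence interval for the QALY difference is too narrow.** The fills are single fixed values with no stated uncertainty method, but the article gives no interval method either. A filled QALY equals the index score, with variance σ². With equal SDs and correlation ρ, a two-point average has variance σ²(1 + ρ)/2, which is 0.65σ² to 0.90σ² for ρ of 0.3 to 0.8. The fill can raise the standard error, so narrowness is not shown.
- **That the HRQoL endpoint is diluted in proportion to the missing scores.** The carry rules stand only in the QALY paragraph. The Abstract defines the HRQoL comparison at 2 months, and no carry rule is stated for it.
- **That the excess per non-returning survivor is 0.18 QALY.** Holding an assumed 2-month score of 0.50 for ten months gives 0.100 + 0.50 × 10/12 = 0.517 against 0.700. That mixes the fill with the omission of month 2 and allows no recovery after surgery.
- **That item 20c adds an error.** It says only "The intention-to-treat (ITT) principle will be applied", which does not fill a missing score. In a condensed article with an analysis plan to follow, that is brevity.

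The promised analysis plan does not excuse the QALY rules themselves, because the article fixes them.

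**Conclusion.** The concern holds for the QALY and cost-effectiveness endpoint. As written, the rules assume no change in health for late deaths and non-returning survivors, and they leave out a 2-month score collected for this analysis: unconditionally for deaths, ambiguously for survivors.

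The direction depends on the patient. Carry-forward overstates QALYs for those who declined and understates them for those who improved; carry-back does the reverse. The sizes are those worked out above: 0.05 to 0.15 QALY per affected survivor, 0.350 instead of 0.267 for a death at month 6, and about 0.005 to 0.015 QALY between arms when missingness differs by 10 points. All rest on assumed utilities and assumed missingness, so the actual bias cannot be found from the documents.

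The primary endpoint, the sample size and the 2-month HRQoL comparison are untouched. The change is worth making before the dataset closes, but the trial's main conclusion does not hang on it.

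**What to change.** Rewrite the QALY paragraph of item 20a, and carry it into the analysis plan, as follows:

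- Calculate QALYs as the area under the curve through index, 2 and 12 months.
- For deaths after the index episode, use the observed scores, hold the last one to the date of death, and count 0 afterwards. The last score is the 2-month score where it exists and otherwise the index score, so for deaths before the 2-month visit the present rule is in effect kept. This is still a single fill, but it uses the latest information on the patient.
- For survivors with a missing index, 2-month or 12-month score, replace carry-forward and carry-back by multiple imputation within arm, using age, sex, CCI, cancer site, CFS-9 and the other EQ-5D scores, pooled by Rubin's rules. CCI belongs in the model because item 20a already names age, sex and CCI as adjustment variables.
- Keep the stated carry rules as a sensitivity analysis.

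The cost is new wording and a modest amount of extra analysis work. No new data are needed.
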